#### **Statistical tests:**

Numerical efficacy endpoints will be formally tested for significance between groups by Analysis of Covariance (ANCOVA). The dependent variable will be the value at each visit, the factor will be the treatment group, and the value at baseline (Day 0) will be the covariate. When the effect of treatment is significant ( $p\text{-value} \leq 0.05$ ), the pairwise Tukey-Kramer post-hoc test will be applied. Significant efficacy of the product, relative to placebo, will be inferred if the coefficient of the treatment group in the ANCOVA model is significantly different from zero ( $p \leq 0.05$ ). Numerical endpoints that are intractably non-normal will be assessed by the Mann-Whitney U test. A within group analysis on efficacy endpoints will be done using the Student's paired t-test or, in the case of intractable non-normality, the Wilcoxon sign rank test.

Probabilities  $\leq 0.05$  will be considered statistically significant. All statistical analysis will be completed using the R Statistical Software Package Version 3.2.1 (R Core Team, 2015) for Microsoft Windows.

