There are numerous proof-of-concept *in vitro* and *in vivo* studies (Bogan & Brenner, 2008; Canto et al., 2012; Khan et al., 2014) that indicate that NR supplementation has beneficial biological effects. However, to date there are no published reports on the safety and bioavailability of NR treatment in humans. We recently conducted a randomized, double-blind, cross-over study to examine the pharmacokinetic effects of Niagen™ dosing in healthy adults ((14NBHC, 2015), unpublished findings). Niagen™ was found to be readily absorbed and exhibit a dose-dependent relationship in human serum and urine. In addition, Niagen™ was well tolerated and presented no toxicity within the acute time-points (1-24h) of the trial. The aim for this study is to investigate the long-term effects of Niagen™ supplementation on Niagen™ metabolite concentrations in blood, urine, and muscle of healthy subjects. Importantly, because urinary N-methylnicotinamide levels are considered the most reliable biomarker for niacin supplementation (Jacob et al., 1998;

Protocol 15NRHC: A randomized, double-blind, placebo controlled parallel study investigating the effects of Niagen™ (Nicotinamide Riboside) on Niagen™ metabolites in healthy adults

Institute of Medicine, 1998), urinary N-methylnicotinamide levels will used as the primary endpoint for assessing Niagen™ metabolism .

Protocol 15NRHC: A randomized, double-blind, placebo controlled parallel study investigating the effects of Niagen™ (Nicotinamide Riboside) on Niagen™ metabolites in healthy adults

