### **Primary outcome:**

The difference in urinary methylnicotinamide levels between placebo and Niagen™ (100mg, 300mg, and 1000mg) treated subjects after 8 weeks of supplementation.

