### **8 STATISTICAL EVALUATION**

#### **8.1 Determination of sample size**

The planned sample size for this study is 140 subjects, with 35 subjects randomized to each treatment group. The primary efficacy endpoint is the change urinary methylnicotinamide levels from baseline to Day 56.

Power calculations were performed to determine the required sample size to provide 80% power at the 0.05 alpha level (that is, to have an 80% chance of obtaining  $p \leq 0.05$  significance).

The sample sizes assume that (1) the basal concentration SD is equal to the end-of-study SD for the placebo group, and (2) the correlation coefficient between baseline and end-of-study values is equal to 0.5.

Based on a previous study by KGK Synergize, the standard deviation of the urinary methylnicotinamide levels was estimated to be 3.1  $\mu\text{M}/\text{mM}$  Creatinine. With an estimated 20% attrition over the course of this study, 80% power and  $p \leq 0.05$  when comparing product to placebo, if the product produces at least a 2.5  $\mu\text{M}/\text{mM}$  Creatinine increase in urinary methylnicotinamide concentration, then a total of 128 subjects are required to be enrolled.

Based on a previous study by Fu et al. (1989), the standard deviation of the erythrocyte NAD levels was estimated to be 10.1  $\mu\text{M}$ . With an estimated 20% attrition over the course of this study, 80% power and  $p \leq 0.05$  when comparing product to placebo, if the product produces at least an 8.7  $\mu\text{M}$  increase in erythrocyte NAD levels, then a total of 140 subjects are required to be enrolled.

Because erythrocyte NAD levels are a secondary endpoint in this study and require a larger sample size, the study was powered on the erythrocyte NAD concentration.

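### The Tukey-Kramer step in section 8.3 adjusts for six pairs where the primary outcome needs three placebo contrasts: a cheap gain in power, not an error

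*Protocol*

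**What the plan says.** The primary outcome in section 2 is "The difference in urinary methylnicotinamide levels between placebo and Niagen™ (100mg, 300mg, and 1000mg) treated subjects after 8 weeks of supplementation". That is three contrasts, each against placebo. The secondary outcomes are framed against placebo as well, and no outcome names a comparison between two doses.

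Under Statistical tests in section 8.3, numerical efficacy endpoints are analysed by ANCOVA with treatment group as a factor and the Day 0 value as covariate. If the treatment effect reaches 0.05, "the pairwise Tukey-Kramer post-hoc test will be applied". The next sentence gives a different rule: efficacy relative to placebo is inferred when the treatment coefficient differs from zero at 0.05. It states no adjustment for three doses.

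Section 8.1 gives the "required sample size to provide 80% power at the 0.05 alpha level", and does so "when comparing product to placebo". The Introduction reports that in an earlier cross-over study the product was found to "exhibit a dose-dependent relationship in human serum and urine".

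**The concern.** Four arms give six pairs. Three are the placebo contrasts that the primary outcome names; the other three compare doses with each other. Tukey-Kramer protects all six, so each placebo contrast has to clear a higher threshold than the question requires and a higher one than the sample size calculation assumed. The procedure also treats the arms as unordered, although the protocol itself reports dose dependence.

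What is at stake is power for the placebo contrasts, and most of all the chance of showing an effect at every dose. The type I error of the Tukey branch is not in question.

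**Working it through.** **Inputs.** From section 8.1: "the standard deviation of the urinary methylnicotinamide levels was estimated to be 3.1" µM/mM creatinine; "if the product produces at least a 2.5" µM/mM increase; baseline to end-of-study correlation 0.5; attrition 20%; alpha 0.05; power 80%. From section 3: 35 per arm. Sidedness is not stated. Two-sided is assumed because it reproduces the plan's total.

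**The plan's own figure.** The change-score SD is 3.1 × √(2 × (1 − 0.5)) = 3.1. Per arm, n = 2 × (1.96 + 0.84)² × 3.1² / 2.5² = 24.1, rounded up to 25. Allowing for attrition, 25 / 0.8 = 31.25, rounded up to 32. Four arms give 128, the stated total for the primary endpoint. The sizing is therefore an unadjusted two-group comparison.

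**Power of one placebo contrast.** Completers per arm: 35 × 0.8 = 28. ANCOVA residual SD: 3.1 × √(1 − 0.5²) = 2.685. Standard error of a contrast: 2.685 × √(2/28) = 0.718. Noncentrality: 2.5 / 0.718 = 3.48. Error degrees of freedom: 4 × 28 − 4 − 1 = 107. Critical t values: Tukey 2.61, Dunnett 2.38, unadjusted 1.98. Power is the probability that a noncentral t exceeds the critical value. The F gate was added by simulation.

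| Case, effect 2.5 | Noncentrality | Gated Tukey | Dunnett, 3 contrasts | First test of a fixed sequence |
|---|---|---|---|---|
| 28 per arm, SD 2.685 | 3.48 | about 81% | 86% | 93% |
| 35 per arm, SD 2.685 | 3.90 | about 90% | 93% | 97% |
| 28 per arm, SD 3.1 | 3.02 | about 65% | about 74% | 85% |

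**Where the 28-per-arm gap comes from** (SD 2.685).
- Dropping the three dose-versus-dose pairs: 86.3 − 80.7 = 5.6 points.
- Using the dose order: 93.2 − 86.3 = 6.9 points, for the first test in the sequence only.
- The F gate: 80.7% without it against 80.6% with it when only 1000 mg works, and 80.6% against 79.5% under a graded response (+1.25/+1.9/+2.5, an assumed shape). That is about one point or less.

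**Larger effects** (28 per arm, SD 2.685; Tukey without the gate, Dunnett, unadjusted). At 3.0: 94.0%, 96.3%, 98.6%. At 3.5: 98.7%, 99.3%, 99.8%. The gap between Tukey and the first test of a sequence falls to about 5 points and then about 1.

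**All three doses** (28 per arm, SD 2.685). If each dose gives +2.5, the chance of showing all three is about 63% with gated Tukey and 85% with the fixed sequence.

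**If the order fails** (28 per arm, SD 2.685). With +2.5 at 100 mg, +2.5 at 300 mg and +1.5 at 1000 mg, the fixed sequence gives 52% for 100 mg and 53% for 300 mg, against about 80% for each with gated Tukey. Dunnett does not use the order, so it stays at 86% for each lower dose.

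**The coefficient rule.** Each placebo contrast is tested at 0.05. Power at 28 per arm and SD 2.685 is 93% without the gate and 86–91% with it. The family-wise error over three such tests is bounded only by 3 × 0.05 = 15%.

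**The case against.** The strongest reply is that nothing here is wrong. An overall test followed by Tukey-Kramer is a valid procedure for four arms, and on the ANCOVA inputs it gives about 80% power, which meets the target in section 8.1. That stands: on those inputs the loss is one of efficiency. On the change-score SD that the sizing used, the branch does fall short, at about 65%; but section 8.3 plans ANCOVA.

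A reader might infer that the plan gives up 13 points of power at 1000 mg. The documents do not support that as a general figure. It needs 28 completers per arm, an effect of exactly 2.5 at that dose, and a comparison with a fixed sequence. Section 8.1 speaks of at least 2.5 and of the product, not of 1000 mg; if response rises with dose, the top dose should do better and the loss there nearly vanishes. The intent-to-treat analysis also carries the last observation forward, which keeps its numbers nearer 35 per arm, where the gap is about 7 points.

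A reader might also take the dose order as established. The Introduction's statement rests on an unpublished cross-over study with time points of 1 to 24 hours, and it does not name methylnicotinamide or levels at 8 weeks. It makes an ordered test reasonable to consider but does not make it safe by default.

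Finally, if the coefficient rule governs, there is no Tukey penalty. That is true, but it exchanges lost power for three placebo tests with no stated error control, so the section still needs one rule.

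**Conclusion.** The mismatch is real and modest. The Tukey branch protects six pairs where the primary outcome needs three, and the sizing assumed none of that adjustment. Limiting the family to the placebo contrasts recovers about 6 points per contrast at 28 per arm, 3 to 4 at 35 per arm, and 8 to 9 on the change-score SD at 28 per arm. Using the dose order would add more for the first dose tested, but only by assuming a monotone response at Day 56. All these figures assume a true effect of 2.5 and a correlation of 0.5.

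The cause is the six-pair adjustment; the overall F test contributes almost nothing. This is a cheap improvement to a valid procedure. It should not be read as an error in the Tukey method or as proof that the trial is underpowered.

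**What to change.** For the Day 56 primary endpoint, replace both decision rules under Statistical tests in section 8.3 with one error-controlled procedure limited to the three placebo contrasts:

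- **Default:** ANCOVA contrasts of each dose with placebo, Dunnett-adjusted at a two-sided family-wise 0.05, with no preceding F gate.
- **Option, if the sponsor accepts a monotone dose response at 8 weeks:** a fixed sequence of 1000, 300, then 100 mg against placebo, each two-sided at 0.05, stopping at the first non-significant result.
- **In either case:** report dose-versus-dose differences with confidence intervals only.

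The choice should be fixed before unblinding. The cost is wording: no extra subjects, samples or visits. The trial gives up formal dose-versus-dose claims. Under the fixed sequence it also gives up any claim for a lower dose when a higher one fails, which is the risk shown in the case where the top dose responds less.

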### 3 STUDY DESIGN

[figure not shown]

This will be a randomized, double blind, placebo controlled, 4-arm parallel study that will investigate the effect of Niagen™ supplements in healthy subjects on Niagen™ metabolite concentrations in urine, blood, and muscle in healthy males and females.

The planned sample size for this study is 140 healthy males or females, with 35 subjects randomized equally to each of the four study arms in a double-blind manner at a ratio of 1:1:1:1.

| Study Arm      | Subject Number |
|----------------|----------------|
| Niagen™ 100mg  | N = 35         |
| Niagen™ 300mg  | N = 35         |
| Niagen™ 1000mg | N = 35         |
| Placebo        | N = 35         |
| Total   | N = 140 |

In order to evaluate primary, secondary, exploratory, and safety outcomes, study assessments will be conducted at baseline and all study visits. At each visit to the clinic, whole blood (which will be centrifuged and separated into WBC, RBC and plasma fractions) and urine will be collected from each participant for NR metabolite and creatinine analysis. REE will also be calculated at baseline and all subsequent clinic visits using indirect calorimetry. A muscle biopsy will be collected at baseline and end of study (week 8).

The study will be conducted at a single site in London, Ontario.

Protocol 15NRHC: A randomized, double-blind, placebo controlled parallel study investigating the effects of Niagen™ (Nicotinamide Riboside) on Niagen™ metabolites in healthy adults

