### 8.3 Analysis Plan

An effectiveness analysis based on the modified intent-to-treat population and an efficacy analysis based on the per protocol population will be performed. Variables will be tested for normality and log-normality. Log-normally distributed variables will be analyzed in the logarithmic domain. Non-normal variables will be analyzed by appropriate non-parametric tests.

All missing values in the intent-to-treat (effectiveness) analysis will be imputed with the most recent previously-available value (LOCF, or "last-observation-carried-forward" imputation). No imputation will be performed for missing values of safety variables.

For each numerical endpoint, a summary table will be prepared with a variety of summary statistics including mean, standard deviation, median, minimum value, and maximum value for each time point-treatment pairing. In order to account for any a priori differences between groups, the summary statistics of the changes from baseline will also be provided. For parameters requiring the logarithmic transformation, the summary statistics will be provided as non-transformed values. Mean values will be displayed as graphs, with a separate line for each product, and error bars indicating  $\pm 1$  SEM. Mean changes from baseline will be graphed similarly.

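### Section 8.3 gives two conflicting rules for declaring a dose effective; the chance of a false claim at Day 56 is about 2.4% or 12.5%, depending on which governs

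*Protocol*

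**What the plan says.** The trial has four arms, "with 35 subjects randomized equally to each of the four study arms in a double-blind manner at a ratio of 1:1:1:1" (section 3). The primary outcome in section 2 compares placebo with each of three doses, "100mg, 300mg, and 1000mg) treated subjects after 8 weeks of supplementation", and section 8.1 places the primary endpoint at Day 56.

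The statistical tests part of section 8.3 sets out an ANCOVA with baseline as covariate: "The dependent variable will be the value at each visit, the factor will be the treatment group". Two consecutive sentences then say how to conclude:

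- The first says that, if the treatment effect has p ≤ 0.05, "the pairwise Tukey-Kramer post-hoc test will be applied" to compare the arms in pairs.
- The second says that "efficacy of the product, relative to placebo, will be inferred if the coefficient of the treatment group in the ANCOVA model is significantly different"; the test is against zero, again at p ≤ 0.05.

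The first rule adjusts for multiple comparisons. The second names no adjustment, no visit and no population. Section 8.3 also plans an effectiveness analysis in the modified ITT population, and "an efficacy analysis based on the per protocol population will be performed". Neither is called primary.

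**The concern.** Only the second sentence says what counts as efficacy against placebo, and it speaks of one product and one coefficient. Treatment is entered as a factor with four levels, so the model has no single treatment coefficient. It has three dose-versus-placebo coefficients, or one overall F-test on three degrees of freedom. An analyst must decide which is meant, and whether the sentence replaces, repeats or follows the Tukey-Kramer step.

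This is not detail that the protocol leaves to a later document. It states both rules, and they can give different answers on the same data. At stake is which of three doses is declared effective on the primary outcome. If the choice is still open at analysis, it can be made after the results are seen.

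**Working it through.** **Inputs.** Four equal arms of 35 (section 3). Alpha 0.05, 80% power, 20% attrition, SD 3.1 and difference 2.5 µM/mM creatinine, baseline to end-of-study correlation 0.5 (section 8.1). Completers per arm: 35 × 0.8 = 28. Two-sided testing is assumed, because the protocol does not state sidedness.

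**The plan's own figure.** SD of change = 3.1 × √(2 × (1 − 0.5)) = 3.1. Per arm, n = 2 × (1.960 + 0.842)² × 3.1² / 2.5² = 24.1, rounded up to 25. Then 25 / 0.8 = 31.25, rounded up to 32, and 4 × 32 = 128, the stated total. This is one unadjusted comparison on change scores. The same 128 also results from an ANCOVA SD of 3.1 × √0.75 = 2.685 with alpha 0.05/3 (n = 24.15, again 25 per arm). So the sample-size section does not settle which rule was intended.

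**False claims if the three coefficients decide.** The three contrasts share the placebo arm, so they correlate at 0.5. With no active dose:

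P(any |z| > 1.96) = 1 − ∫ [Φ(x + 1.96√2) − Φ(x − 1.96√2)]³ φ(x) dx = 0.125.

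With the exponent 2 (two inactive doses, the third active) it is 0.091. Simulation with t-statistics on 4n − 5 degrees of freedom gives 12.4% at 28 per arm and 12.5% at 35.

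**All readings, Day 56, one population (simulation, 28 per arm, 107 df):**

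| Reading of section 8.3 | No dose works: any false claim | One dose works: false claim for the other two |
|---|---|---|
| Three unadjusted coefficients | about 12.5% | about 9% |
| Same, only after a significant F-test | about 4% | about 9% |
| F-test, then Tukey-Kramer | about 2.4% | about 2.0% |

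The F-test protects the unadjusted coefficients only while no dose works. Once one dose is active the gate is nearly always open, and the other two are tested without protection.

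**Where the two rules part.** Standard error of a difference = 2.685 × √(2/28) = 0.718. Critical values on 107 df are 1.982 unadjusted and 2.610 for Tukey-Kramer. In difference units these are 1.982 × 0.718 = 1.42 and 2.610 × 0.718 = 1.87. An adjusted difference between about 1.42 and 1.87 is effective under one sentence and not under the other.

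**Power for a true difference of 2.5.** Noncentrality = 2.5 / 0.718 = 3.48. The noncentral t gives 93% unadjusted, 86% with Dunnett (critical value 2.386) and 81% with Tukey-Kramer. In simulation, the unadjusted coefficient and gated Tukey-Kramer disagree on an active dose in about 13% of trials, which matches 93% − 81% = 12% plus rounding and the effect of the gate.

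**The case against.** The strongest defence is that the two sentences can be read in sequence: the F-test at 0.05, then Tukey-Kramer to locate the doses, with the singular coefficient merely restating the overall test. On that reading the error is controlled: 5.0% for the overall test and about 2.4% for any dose against placebo. This much stands: one of the two written rules is sound, and no text gives the other precedence. A reader might infer that the plan simply has a family-wise error of 12% or more. The document does not support that. The figure holds only if the sentence means three coefficients and overrides the one before it. The defence does not remove the conflict, however. A significant overall test does not show which dose differs from placebo, or that any does, so it cannot carry the conclusion that the sentence draws.

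Three other stronger readings also fail:

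- **All visits count.** The model is run at each visit, but sections 2 and 8.1 fix the primary outcome at 8 weeks (Day 56). Earlier visits do not add to its error rate.
- **Success in either population counts.** Section 8.3 plans both analyses but does not say that either suffices. Any error figure for that reading would need a per-protocol fraction that the document does not give.
- **Tukey-Kramer is an error.** It adjusts for six pairs where the stated outcomes need three, but it keeps about 81% power against a target of 80%, and comparing doses is a legitimate interest. It is a valid choice.

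**Conclusion.** The point holds as a contradiction in the decision rule for the primary outcome. For Day 56 in one population, the chance of falsely declaring some dose effective is about 2.4% or about 12.5%, according to which sentence governs, and about 4% to 9% if the coefficients are read behind the F-test. The two rules disagree on a truly active dose in about 13% of trials.

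The error rates assume two-sided tests, equal arms and normal errors. They hardly depend on arm size between 28 and 35. The power and disagreement figures also rest on the protocol's SD of 3.1, difference of 2.5, correlation of 0.5 and 20% attrition. The finding does not show that the error will exceed 5%, only that the text permits it.

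**What to change.** Delete the coefficient sentence in section 8.3 and state one rule, for example:

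*Efficacy of a dose on the primary outcome is inferred only if its Tukey-Kramer-adjusted comparison with placebo, from the Day 56 ANCOVA in the modified ITT population, has p ≤ 0.05. The per-protocol analysis and the earlier visits are supportive for this claim.*

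Use one name for that population, since section 8.2 defines it as ITT and section 8.3 calls it modified ITT.

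Extend the adjustment to the Mann-Whitney fallback. It is a two-group test, so with four arms it too becomes several unadjusted comparisons.

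An optional improvement is Dunnett's adjustment without the F-test gate, which matches the stated product-versus-placebo comparisons. It raises power from about 81% to about 86% at the planning values. Its price is that dose-versus-dose contrasts become descriptive.

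Either version is a wording change only. It needs no more subjects or data: Tukey-Kramer already gives about 81% power for the primary outcome with 28 completers per arm.

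### The fallback for non-normal endpoints is a two-sample Mann-Whitney test in a four-arm trial, with no error control across arms and no baseline covariate

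*Protocol*

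**What the plan says.** Section 3 of the protocol sets the design: "This will be a randomized, double blind, placebo controlled, 4-arm parallel study", "with 35 subjects randomized equally to each of the four study arms in a double-blind manner at a ratio of 1:1:1:1".

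Section 8.3 first checks each variable for normality and log-normality and analyses log-normal variables on the log scale. For the rest it says: "Non-normal variables will be analyzed by appropriate non-parametric tests". The part headed Statistical tests then gives two routes for comparing groups:

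- **Parametric route.** ANCOVA of the value at each visit, with treatment group as the factor, where "the value at baseline (Day 0) will be the covariate". If the treatment effect is significant at 0.05, "the pairwise Tukey-Kramer post-hoc test will be applied".
- **Fallback.** "Numerical endpoints that are intractably non-normal will be assessed by the Mann-Whitney U test".

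The fallback sentence does not say which arms are paired, whether the visit value or the change from baseline is ranked, whether a test across all arms comes first, or whether any p-value is adjusted. The general threshold of 0.05 applies.

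**The concern.** A Mann-Whitney test cannot answer one question about four arms. It has to be repeated, either three times (each dose against placebo) or six times (all pairs). As written, each repeat is judged at 0.05 with nothing in front of it and no correction after it. The same endpoint, asked the same question, would be held to a different error standard depending on a distribution check made after the data are in.

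The fallback also has no baseline covariate. The Day 0 value is collected for every efficacy endpoint and the parametric route uses it, so the fallback forgoes the precision that adjustment would bring. The sentence is not limited to minor endpoints and could apply to urinary methylnicotinamide, the primary outcome.

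**Working it through.** **Inputs.** All are from the protocol: four arms of 35 (section 3); and from section 8.1, "to provide 80% power at the 0.05 alpha level", "the standard deviation of the urinary methylnicotinamide levels was estimated to be 3.1" (µM/mM creatinine), a difference of 2.5, a correlation of 0.5 between baseline and end of study, and 20% attrition. Sidedness is not stated; two-sided is assumed because it reproduces the plan's figure.

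**Reproducing the plan's figure for the primary endpoint.**
- SD of change = √(2 × 3.1² × (1 − 0.5)) = 3.1.
- n per arm = 2 × (1.96 + 0.842)² × 3.1² / 2.5² = 24.1, rounded up to 25.
- 25 / 0.8 = 31.25, rounded up to 32; 4 × 32 = 128, as stated.

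The trial enrols 35 per arm, so 35 × 0.8 = 28 completers per arm are used below.

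**Family-wise error, no true effect in any arm, each test at 0.05.**
- If the tests were independent: 1 − 0.95³ = 0.143 for three and 1 − 0.95⁶ = 0.265 for six. Tests that share arms are correlated, so the real figures are lower.
- Simulation, 20,000 runs: 0.119 (three) and 0.198 (six) at 28 per arm; 0.127 and 0.204 at 35 per arm. Further simulations at 28 and 33 per arm stayed within 0.12-0.13 and 0.19-0.21. The test uses only ranks, so apart from ties the shape of the distribution does not matter.
- For comparison, an F test at 0.05 followed by Tukey gives 0.043 for any pair (28 per arm, normal data, 40,000 runs, simulated without the covariate).

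**Power for one dose against placebo** at 28 per arm and an effect of 2.5/3.1 SD (6,000 runs, normal data, unadjusted 0.05):

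| Correlation | Mann-Whitney, final value | Mann-Whitney, change | Rank ANCOVA | ANCOVA |
|---|---|---|---|---|
| 0.3 | 82% | 69% | 85% | 87% |
| 0.5 (protocol) | 82% | 82% | 90% | 92% |
| 0.7 | 80% | 96% | 97% | 98% |

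The rows for 0.3 and 0.7 are assumed values that show the range. At 0.05/3 and correlation 0.5, Mann-Whitney has about 67-68% and rank ANCOVA 80-82%.

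**Against the route actually planned.** With only the top dose active and correlation 0.5, ANCOVA with the F test and Tukey step has about 80-81%, and unadjusted Mann-Whitney 81-82%. If the same data are made skewed and left untransformed, ANCOVA with Tukey falls to 63% while Mann-Whitney stays at 82%.

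**After repair.** Bonferroni over the three placebo comparisons gives a family-wise error of 0.040-0.043. A Kruskal-Wallis test placed before unadjusted pairwise tests gives 0.038-0.040 (three) or 0.049 (six). That protection holds only when no dose has any effect, so the pairwise tests still need their own adjustment.

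**The case against.** Several points on the other side are sound.

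- **Loss of power against the plan.** A reader might infer that an endpoint sent to the fallback loses power relative to the planned analysis. It does not: unadjusted Mann-Whitney matches ANCOVA with Tukey-Kramer and beats it on skewed data. It keeps pace only by omitting the multiplicity control. The fair comparator for non-normal data is a rank test with baseline adjustment at the same alpha, and there the loss is real.
- **Likely users.** hsCRP and the creatinine-standardised metabolites look like candidates because such measures are often skewed. The protocol gives no distribution data, and the log step comes first. They are possible users, no more.
- **Baseline information.** Section 8.1 describes the primary endpoint as a change from baseline, and ranking the change would use baseline in part. What is certainly absent is covariate adjustment. At correlation 0.5, ranking the change gains nothing over ranking the final value.
- **The contrast between routes.** Section 8.3 also infers efficacy from the ANCOVA treatment coefficient at 0.05, with no stated adjustment. Applied to three dose coefficients without the F test, that gives a family-wise error of 0.123, against 0.120 for Mann-Whitney in a matching simulation. The parametric route is cleaner only if its treatment test and Tukey-Kramer step govern.
- **An unseen SAP, or the general wording.** An SAP might add an adjustment, and section 8.3 does speak of suitable non-parametric tests. But the protocol then names the between-group test, and the named test does not fit four arms.

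**Conclusion.** The point stands in limited form. The protocol fixes a two-sample test as its only between-group fallback in a four-arm trial, with no test across arms, no adjustment and no baseline covariate. It would be wrong to say that the 5% level of each test is broken, or that 0.05 was promised as a family-wise rate. What is uncontrolled is the chance of at least one false positive across the arms: about 12-13% for three comparisons with placebo and 19-21% for six pairs.

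At matched alpha the power cost against a baseline-adjusted rank test is about 82% versus 90% at 0.05, and about 67% versus 80-82% at 0.05/3. These figures assume 28 per arm, the protocol's effect and SD for the primary endpoint, and its correlation of 0.5; a lower correlation shrinks the gain from adjustment. How much this matters depends on which endpoints reach the branch, which the protocol does not show. The wording leaves the primary endpoint exposed, so the sentence should be changed.

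**What to change.** Replace the fallback sentence with: endpoints that remain non-normal after log transformation are analysed by rank ANCOVA (ranks of the visit value adjusted for ranks of the Day 0 value, Quade's method) across the four arms at 0.05, followed by pairwise comparisons with Holm adjustment. The text should say which pairs are compared. This parallels the treatment test and Tukey-Kramer step of the parametric route.

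At minimum, use Kruskal-Wallis followed by Holm-adjusted pairwise Mann-Whitney tests. That controls the error but does not recover the baseline information.

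The cost is one sentence, with no new data and no change of software, since it needs only ranking and linear regression in R. Power per comparison is slightly lower than with unadjusted testing. Rank ANCOVA reaches 80-82% at 0.05/3, which is a floor for Holm over the three placebo comparisons before any loss from the test across arms. With an F test and Tukey step over all pairs it reaches about 77%. Unadjusted Mann-Whitney has 82%. The minimum version costs more, since Mann-Whitney at 0.05/3 has about 67-68%.
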